### Outcomes

#### Primary outcome

##### Understanding

We define understanding as the comprehension of key guideline content (e.g., year of publication, intent of recommendation, direction of recommendation, etc.). This outcome will be measured using seven multiple-choice questions about key concepts in the recommendation with four to six response options for each question and only one correct answer (total minimum score of 0, maximum score of 7). Based on previous work, we aim to detect a difference of 10% in understanding between groups which we consider an important difference (an average difference of 1 correct answer) [18, 19, 21–23].

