### Statistical analysis

Only participants who submit a complete good quality survey will be included in the analysis. We will exclude all incomplete, speeding (less than 6 min to completion), and straight-lining responses. Each population’s results will be analyzed separately, and we will explore subgroup effects within each group. These subgroups are the topic of recommendation, health literacy level, and English proficiency level of participants. We will also pool the results across populations and conduct a meta-analysis for our primary outcome of “understanding” and other secondary outcomes. In the final analysis, after pooling the results, we will explore for potential interaction related to the recommendation topic and participants’ health literacy level. We will conduct the analyses using IBM SPSS® (Statistical Package for Social Sciences) version 23.

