#### Inferential analysis

We will perform a primary analysis including all randomized participants. We will exclude participants who take less than 6 min to complete the survey. For the outcome of understanding, we will use *χ*^2^ tests and risk difference with 95% CIs to compare the proportion of correct responses between groups. For the outcomes of accessibility and satisfaction, we will use *t*-tests and mean differences 95% confidence intervals (95% CIs) to compare means and SDs between the intervention and control groups. Finally, we will present preference as mean (SD) overall and for both trial arms. Skewness, Shapiro-Wilk tests, and histograms will be used to evaluate whether the distribution was shifted toward the same preference in both groups. Levene’s test of equal variances will be used for all *t*-tests and degrees of freedom will be adjusted for *p* < 0.05. We will report all *p*-values to three decimal places, with values less than 0.001 reported as < 0.001. We will consider statistical significance at *p* < 0.05. Furthermore, we will conduct a meta-analysis across the three trials by combining results of the three trials. Our a priori hypothesis is that there is no difference across the three populations despite the differences in population characteristics and slight difference in the presentation formats for each population. However, we will explore differences between trials applying the GRADE approach to evaluating inconsistency which includes the chi-square test, the *I*^2^ value, the overlap in confidence intervals, and the differences in the point estimates of effect for all outcomes [29].

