## Reporting

We will report our quantitative findings according to the Consolidated Standards of Reporting Trials (CONSORT) reporting guidelines and qualitative findings following the Consolidated criteria for reporting qualitative research (COREQ) [36, 37]. For the quantitative results, we will pool the results across the three populations and conduct a meta-analysis for our primary outcome of “understanding” and other secondary outcomes. We will explore results for each population separately as well as compare results across populations.

Finally, we will crossmatch and compare the results of the qualitative interviews with those of the quantitative surveys and try to better understand and contextualize the RCT findings. Based on the results, we will discuss possible changes to the PLR format.

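### The heterogeneity tools named for the hypothesis of no difference across adults, parents and youth give no interval for that difference, and a quiet result cannot support it

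*Protocol article*

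**What the plan says.** The Inferential analysis section plans to pool: "we will conduct a meta-analysis across the three trials by combining results of the three trials". It then gives the expectation about the three trials: "Our a priori hypothesis is that there is no difference across the three populations despite the differences in population characteristics". The next sentence sets out how this will be examined: "However, we will explore differences between trials applying the GRADE approach to evaluating inconsistency". It describes that approach as one "which includes the chi-square test, the *I*^2^ value, the overlap in confidence intervals, and the differences in the point estimates of effect for all outcomes".

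Two other places bear on the point. The Statistical analysis section says: "Each population’s results will be analyzed separately, and we will explore subgroup effects within each group". The Reporting section promises: "We will explore results for each population separately as well as compare results across populations".

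The article gives no interval for a between-population difference. The only size it calls important is in the Understanding section ("we aim to detect a difference of 10% in understanding between groups which we consider an important difference"), and that refers to PLR versus SLV within a trial.

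**The concern.** The stated hypothesis is one of equality, which is also the null hypothesis of the heterogeneity chi-square. With three of the four tools (chi-square, I-squared, CI overlap), no difference is what appears when the tool detects nothing. The fourth, the spread of point estimates, shows size but carries no uncertainty.

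Each trial is sized for its own PLR-versus-SLV comparison, not for differences between trials. If the PLR benefit were smaller or absent in one population, the check could stay quiet while the pooled benefit was clear. The article itself notes that the populations differ in characteristics and slightly in presentation format, so unequal effects are plausible. What is at stake is the comparison across populations promised under Reporting and how far the pooled estimate may be generalised. No single trial's primary result is affected.

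**Working it through.** **Inputs.** From Sample size calculation: 75% PLR, 60% SLV, 120 per arm, three trials. From Understanding: seven items, score 0–7. From Inferential analysis: significance at p < 0.05. Assumptions: the pattern of effects across populations, the same SE in each trial, and an inter-item correlation r of 0.1 to 0.3 for the score.

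**The plan's own figure.** The article gives no figure for the cross-population comparison. Its 240 per population does not reproduce under the stated two-sided test: the usual two-proportion formula gives 152 per arm two-sided, and 120 per arm only one-sided. That is a separate matter; 120 per arm is taken here as planned.

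**Binary basis (one result per participant).**
- SE of each risk difference = √(0.75×0.25/120 + 0.60×0.40/120) = 0.0597, or 5.97 points.
- Heterogeneity chi-square on 2 df: noncentrality λ = Σ(effect − mean)²/SE².
- One population 10 points lower (15/15/5): λ = 0.00667/0.00356 = 1.87. Power is 21% at 0.05, so the miss rate is 79% (68% at the 0.10 level).
- 15/15/0: λ = 0.0150/0.00356 = 4.21. Power is 43%, so the miss rate is 57% (44% at 0.10).
- All three 95% CIs overlap in about 90% and 74% of simulated runs respectively.
- I-squared is below 50% in about 62% and 38%.

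Arm-specific variances and evenly spread effects lower the power slightly, to 17–20% for 10 points and 34–41% for 15.

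**Why CI overlap is the weakest item.** With equal SEs, two 95% CIs separate only when the estimates differ by 2×1.96 = 3.92 SE, which is 23.4 points. A direct 5% test of the same difference needs 1.96×√2 = 2.77 SE, which is 16.5 points.

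**Precision of a direct contrast.** Half-width = 1.96×√2×5.97 = 16.5 points.

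**Score basis.** The SE on the proportion scale is multiplied by √((1+6r)/7). The score SD is √(7×0.21375×(1+6r)), where 0.21375 is the mean of 0.1875 and 0.24.

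| r | SD of score | SE (points) | Miss, 15/15/5 | Miss, 15/15/0 | Contrast half-width (points) |
|---|---|---|---|---|---|
| 0.1 | 1.55 | 2.85 | 27% | 2% | 7.9 |
| 0.2 | 1.81 | 3.35 | 42% | 8% | 9.3 |
| 0.3 | 2.05 | 3.77 | 52% | 16% | 10.5 |

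With arm-specific variances and evenly spread effects included, the miss rates over this range of r are 30–63% for 10 points and 3–28% for 15. If items were independent (r = 0), the 10-point miss rate would be about 9%.

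**Consequence for the pooled result, binary basis, 15/15/0.** The pooled effect is 10 points with SE 5.97/√3 = 3.45 and power about 83%. A significant pooled benefit together with a non-significant chi-square occurs in about 0.565×0.83 = 47% of trial sets, although one population has no benefit.

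**The case against.** The strongest reply is that the plan never says a quiet check proves consistency. It states an expectation, then turns to exploring departures from it. It lists four items to be read together, and gives each population its own risk difference and CI. All of that stands. A reader might infer that non-significance will be taken as consistency and the pooled benefit then applied to a population without one. No section says so, and the separate results would show such a population.

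The single-item miss rates also overstate how often the whole list would be quiet. On the binary basis, take quiet to mean chi-square non-significant, I-squared below 50%, all CIs overlapping and estimates within 10 points (the I-squared and spread cut-offs are assumed). This occurs in about 13% of 15/15/0 runs and 28–29% of 10-point runs. The spread item earns much of that by being noisy: estimates range over 10 points or more in 46% of runs with no true difference.

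A further reply is that margins and thresholds may sit in the full protocol or analysis plan. That is fair, and their absence is not the point. The article itself names a hypothesis of equality and the tools to judge it, and those tools cannot support it.

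**Conclusion.** The point holds as a limited one. The listed tools can suggest that the PLR effect differs between populations; they cannot show that it does not, and none puts an interval on the difference. For a 10-point difference in one population the chi-square is weak on both bases: missed about 79% of the time on the binary planning basis, and about 27–52% on the 0–7 score at r = 0.1 to 0.3.

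A tempting stronger statement is that a 15-point difference would also often go unnoticed. That holds only on the binary basis (57%); on the score the miss rate is about 2–16%. The article does not settle the choice of basis: it scores seven items per participant but gives planning rates of 75% and 60% correct. The correlation and the pattern of effects are assumptions.

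A reader might also take the 10 points in the Understanding section as an equivalence margin. It is defined for PLR versus SLV, and a CI with half-width 16.5 points can never lie within ±10. Only the secondary cross-population conclusion is affected.

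**What to change.** In Inferential analysis:

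1. Keep the GRADE inconsistency items as description.
2. Replace CI overlap, as the means of comparison, with the population-by-format contrasts (adult–parent, adult–youth, parent–youth) and their 95% CIs.
3. State in advance that a non-significant chi-square, a low I-squared or overlapping CIs will not be reported as evidence that the effect is the same in all populations.

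Do not impose 10 points as a similarity margin. If the sponsor wants to conclude similarity, it should set and justify its own margin for differences between populations; on the binary basis, any margin below about 16.5 points could not be met.

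The cost is three extra contrasts from data already collected and a few sentences of text, with no more participants. The downside is that cross-population consistency will probably be reported as inconclusive, certainly so for moderate differences if the binary basis applies. On the score basis, half-widths of about 8 to 10.5 points would make the contrasts more informative.

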### Qualitative methods

We will interview a sample of survey participants to explore their user experience with two recommendation formats. These semi-structured interviews will help us contextualize the results of the survey and understand participants’ preference for receiving the information.

#### Selection of participants

At the end of each survey, participants will be invited to contribute to a virtual, one-on-one, semi-structured interview, conducted by the research coordinator for each leading site. Interested participants will voluntarily provide their email address at the end of the survey, and the research coordinator will follow up with them through email.

#### Interviews

We will invite individuals from the list of participants who have agreed to participate in the qualitative interviews. For the parents’ population, we will use purposive sampling (inviting participants based on region, ethnicity, gender, and topic of recommendation). For the adult and youth populations, we will not use a purposive sample; however, we will collect demographic data from the participants at the time of the interview. All interview participants will be compensated for their time with a gift card valued at $25 CAD.

Prior to the interview, participants will be provided with the consent form for the semi-structured interviews. Following that, a Zoom invite will be shared with the participant. Prior to the start of the interview, the research coordinator conducting the interview will obtain verbal consent from the participant for participating in the interview and for the interview to be audio-recorded. If the participant chooses to leave their video camera on during the interview, consent will be acquired for video-recording the interview. Consent will be documented on a log by the coordinator. If participants decline recording of the interviews, we will not move forward with the interview. We will transcribe interview recordings verbatim and de-identify all interview transcripts.

Interviews will be conducted in English by trained interviewers and will take approximately 30–60 min. Interviews will be guided by open-ended questions that cover the seven facets of the honeycomb model to verify user’s experiences with the different recommendation formats: usefulness, usability, findability, accessibility, desirability, credibility, and value [30]. We will pilot test the interview guide within the three populations to refine the questions and language based on the populations’ unique needs prior to the interviews.

#### Data management

All recordings will be stored on a password-protected device and secure network and accessed only by members of the research team. The recordings will be kept for 5 years, at which point they will be destroyed. All transcribed recordings will be reviewed and verified by the interviewer or a second research team member prior to being de-identified. NVivo software (QSR, 2018) will be used for data coding and management.

#### Data analysis

Qualitative data analysis will follow a hybrid inductive/deductive method [31]. This method allows for flexibility to utilize an established framework during analysis (deductive) as well as identify codes that emerge from the data (inductive). The 7 elements of the honeycomb model for user experience (Fig. 4) informed the creation of the interview guide and were adapted and used as the initial model for analysis (see Supplementary Material 2 for the interview guide) [30]. The seven elements of the model will guide coding with inductive coding of data that extends beyond the model.

**Fig. 4 Fig4:**
[figure not shown]
The honeycomb model of user experience

Data collection and analysis will occur iteratively [32]. The analysis will follow six steps: (1) data cleaning-comparing the transcript with the recording and doing the cleaning to ensure alignment, (2) generating initial codes using line-by-line coding, (3) searching for themes guided by the honeycomb model, (4) reviewing the themes and generating a “thematic map,” (5) defining and naming themes guided by the honeycomb model, and (6) writing the report. Data collection will occur until saturation is reached [33].

We will develop joint displays, explicitly merging the results from the three populations’ data sets through a side-by-side comparison to assess how findings are aligned among the three data sets [34].

#### Rigor

Strategies for maintaining rigor [35] will be used such as utilize a detailed study log and audit trail to ensure transparency. A coding system will be utilized and refined throughout the iterative data collection and analysis stages and each site will have a primary coder and a secondary coder to code approximately 10% of the transcripts and compare to maintain intra-rater reliability [35]. We will use iterative member checking, reflecting back statements made during interviews to participants for clarity and understanding.

We will also use our trial survey data to triangulate our findings with survey responses. Our analysis team will reflect on and disclose our own digital experiences and consider this in our iterative analysis process.

## Reporting

We will report our quantitative findings according to the Consolidated Standards of Reporting Trials (CONSORT) reporting guidelines and qualitative findings following the Consolidated criteria for reporting qualitative research (COREQ) [36, 37]. For the quantitative results, we will pool the results across the three populations and conduct a meta-analysis for our primary outcome of “understanding” and other secondary outcomes. We will explore results for each population separately as well as compare results across populations.

Finally, we will crossmatch and compare the results of the qualitative interviews with those of the quantitative surveys and try to better understand and contextualize the RCT findings. Based on the results, we will discuss possible changes to the PLR format.

## Discussion

Guideline developers typically create recommendations for health professionals or health agencies [1]. However, particularly in the context of COVID-19 and any future pandemics or topics of high public interest, the general public must have access to health recommendations that they can understand and trust [38]. For example, public understanding and acceptance is required for the implementation and uptake of many public health recommendations such as vaccination, using facial masks, and social distancing. Furthermore, parents are making decisions for children who cannot make decisions for themselves, and they need trustworthy recommendations specific to this unique population (e.g., vaccine safety and efficacy for children). On the other hand, youth access health recommendations about COVID-19 and make independent decisions about implementing public health measures, like social distancing and face mask use [3].

It has become crucial to engage end-users in shaping behaviors and activities that will eventually affect them and their communities. Their involvement will improve the relevance, usefulness, and transparency of guidelines [39]. More importantly, it will ensure that these guideline products are understandable and acceptable. We believe that when the public is presented with plain language recommendations, they will have a better understanding of guideline recommendations. These trials are designed with the input of end-users from three populations: youth, adults, and parents. Results will inform the best ways to make recommendations understandable and accessible to the public, thus increasing the public’s confidence in science and evidence uptake.

## Trial status

Protocol version 1, May 3, 2022

Started recruitment: May 26, 2022

Estimated recruitment completion: October 31, 2022

## Data Availability

Anonymous survey data will be publicly available from an open-access online repository to be chosen within 2 years of data collection. The datasets analyzed during the current study and statistical code are available from the corresponding author on reasonable request, as is the full protocol.

## Abbreviations

CAD: Canadian Dollars
CIHR: Canadian Institutes of Health Research
CONSORT: Consolidated Standards of Reporting Trials
COREQ: Consolidated Criteria for Reporting Qualitative Research
COVID-19: Coronavirus disease of 2019
GIN: Guidelines International Network
HiREB: Hamilton Integrated Research Ethics Board
KM: Knowledge mobilization
PLR: Plain language recommendation
RecMap: COVID-19 Living Map of Recommendations and Gateway to Contextualization
RCT: Randomized controlled trial
SLV: Standard language version
